### Trial design

2.2

This is a multicenter, single-blind, randomized controlled trail that participants will be random allocated to 3 groups with a 1:1:1 allocation ratio. The 3 groups are acupuncture group (AG), sham acupuncture group (NAG), and waiting-list group (WLG). The flowchart of the trial design is shown in Figure 1.

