### Sample size and statistical methods

7.5

The sample size calculation is based on the improvement of Montreal cognitive assessment scale (MoCA) scores, which has a higher sensitivity than MMSE for MCI.^[7]^ According to the similar published articles,^[40]^ the mean difference in MoCA scores between AG and control group (CG) is 1.5, with a standard deviation of 1.13 in AG and 1.20 in CG. According to our previous study, acupuncture treatment can probably improve the MoCA by 0.6 on average compared with control group. Considering a 1-sided significance level of 0.025 and power of 95%, 95 participants are required for each group, as calculated by PASS 11 software. To minimize attrition bias, we assumed the dropout rate of 20%, making it necessary to include at least 357 participants with a 1:1:1 group allocation rate. We plan to enroll 360 participants in total.

Continuous variables are presented as mean (SD) if they obey normal distribution, and paired-sample *t* test will be used in intragroup comparison; if they are not normal distribution, median (quartile interval) [M(IQR)] will present them, and Wilcoxon rank sum test will be used in intra-group comparison; Variance analysis will be used for comparison between groups which is consistent with the normal distribution and homogeneity of variance; if not, then Mann–Whitney *U* test will be used. Group comparisons will then be undertaken using χ^2^ tests for categorical characteristics. Two-sided *P* < .05 represents statistical significance for all the analyses.

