## Discussion

8

By reason of the high prevalence of PSCIND and high social acceptability of acupuncture in China, we have the advantage on conducting large-sample research. This protocol design also has additional strengths. First, as far as we know, we are the first randomized controlled trial to study if acupuncture has efficacy on preventing PSCIND progressing to PSD; second, avoiding false increase of patients’ cognitive-function test results caused by multiple use of same scale. We measure the cognitive function with different version of MoCA, including 7.1, 7.2, 7.3, and basic of MoCA; third, multicenter. Our trial will be conducted in 5 inpatient and outpatient stroke rehabilitation units of different cities, which can ensure the sample representativeness. Fourth, a 12-week intervention and 24-week follow-up assessment can provide reliable long-term effect evidence for acupuncture on improving cognitive function, mental state, and quality of life for PSCIND patients.

On the contrary, this protocol design also has limitations, which are as follows. There could be a very few overlaps exists between early stage of AD and PSCIND in our participants. Fifty-six percent of all demented cases are the patients who suffer from AD with stroke.^[41]^ A Study also shows that the atherosclerosis, which is one of the common causes of stroke, may also have effects on the pathogenesis of AD.^[42]^ We can see that the inner correlation may exist between stroke and AD. Therefore, the participants in our trail may also suffer both AD and PSCI. And this will affect the evaluation of the outcome in this study. Potential spontaneous recovery at the early stage of stroke may have the confounding effects on this trial, but the waiting-list group can reduce the effects of it. Due to the limitations of equipment and capital, only part of the participants will get the fMRI scan. This may affect the generalizability of the results.

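### Both non-parametric fallback tests in section 7.5 misfit the design: a rank-sum test for paired before-after data, and a two-sample Mann–Whitney test for three arms

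*Protocol article*

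**What the plan says.** All of the relevant rules stand in the protocol article, section 7.5 (Sample size and statistical methods).

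- Within a group, normal data: "paired-sample *t* test will be used in intragroup comparison".
- Within a group, non-normal data: "Wilcoxon rank sum test will be used in intra-group comparison".
- Between groups, normal data with equal variances: "Variance analysis will be used for comparison between groups".
- Between groups, otherwise: "if not, then Mann–Whitney *U* test will be used".
- Significance: two-sided 0.05 for every analysis. No pairs are named and no adjustment is stated.

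Two design facts bear on these rules. Section 2.2 (Trial design) states that "participants will be random allocated to 3 groups with a 1:1:1 allocation ratio". Section 3.5 and Table 3 have the same patients assessed at baseline and at 12, 24 and 36 weeks.

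**The concern.** Each fallback should answer the same question as the parametric test it replaces. Neither does.

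**Within groups.** The parametric choice is a paired test, and the visit schedule confirms that the data are paired. The rank-sum test is for two independent samples. Its non-parametric paired counterpart is the signed-rank test. An analyst who follows the text literally would discard the pairing.

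**Between groups.** Analysis of variance tests three arms at once. A single Mann–Whitney test takes two. The fallback therefore yields either no overall test or a set of pairwise tests. The section does not say which pairs would be tested or how they would be combined, while it sets an unadjusted 0.05 for everything.

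At stake are real within-group changes that go undetected, and a between-group error rate above the stated 5% whenever the fallback is used.

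**Working it through.** The plan states no figure for the behaviour of these tests, so there is none to reproduce. The check asks how the named tests behave at the plan's own size.

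**Inputs from the plan:** 95 evaluable patients per group (section 7.5), three arms at 1:1:1 (section 2.2), two-sided 0.05 (section 7.5).

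**Assumed inputs, not in the documents:** before-after correlation r from 0 to 0.8; rounded, MoCA-like scores with mean 21 and SD 3. A change of 0.2 SD is then 0.2 × 3 = 0.6 points.

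**Step 1: why ignoring the pairing is conservative.** For a difference of means with equal SD σ, the true variance is 2σ²(1 − r)/n, but an unpaired test assumes 2σ²/n. The true size at a nominal 5% is therefore about 2[1 − Φ(1.96/√(1 − r))].

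- r = 0.5: 1.96/√0.5 = 2.77, size 0.56%.
- r = 0.7: 1.96/√0.3 = 3.58, size 0.035%.

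This is normal theory for means, and only a guide to the rank-sum test, so the rank tests were simulated directly.

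**Step 2: simulated rejection rates at nominal 5%, n = 95** (10,000 runs for rank-sum, 3,000 for signed-rank).

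| r | No change: rank-sum | No change: signed-rank | 0.2 SD change: rank-sum | 0.2 SD change: signed-rank |
|---|---|---|---|---|
| 0 | 5.0% | 5.2% | 27% | 28% |
| 0.3 | 2.4% | 5.1% | 23% | 36% |
| 0.5 | 0.6% | 5.2% | 19% | 47% |
| 0.7 | 0.06% | 5.5% | 14% | 69% |
| 0.8 | 0 of 10,000 | 5.7% | 11% | 84% |

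The signed-rank test stays close to 5% throughout. The rank-sum test rejects too rarely as soon as r is positive, and loses more power as r rises.

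**Step 3: three arms, no true difference, 95 per arm, 10,000 runs.**

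| Procedure | False-positive rate |
|---|---|
| Each pairwise Mann–Whitney test by itself | 4.7% to 5.0% |
| At least one of two (acupuncture against each control), unadjusted | 8.4% |
| At least one of three pairs, unadjusted | 11.9% |
| At least one of three pairs, Bonferroni (0.05/3 each) | 4.0% |
| Kruskal–Wallis, overall | 4.5% |
| Kruskal–Wallis significant, then at least one pair at 0.05 | 4.5% |

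For comparison, three independent tests would give 1 − 0.95³ = 14.3%. The simulated 11.9% is lower because the pairs share arms.

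**The case against.** **Slip of the pen.** Since the rank-sum test stands beside a paired t test, the authors may have meant signed-rank. That is plausible, but the document does not confirm it, and the text as written names the wrong test.

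**The fallbacks may never be used.** They apply only if normality fails or, between groups, if variances are unequal. No score distributions are given. The rule opens with continuous variables and sends categorical ones to χ², so it is unclear where a coarse scale such as the CDR falls. The primary outcome of dementia incidence is binary and unaffected. This stands, and it limits the weight of the point. It does not remove it: eligibility cuts off both MoCA and MMSE at baseline (section 2.3), so non-normal scores are a realistic prospect.

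**Post-hoc procedure belongs in the analysis plan.** Partly true, and that plan is not shown. But the article does more than stay silent: it names a two-sample test for three arms and sets one unadjusted threshold for everything.

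**Stronger readings that the documents do not support:**

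- *That all P values from these tests would be invalid or would produce false positives.* With positive correlation the rank-sum error runs the other way, and each pairwise Mann–Whitney P value holds its level. The excess arises only when several pairs are tested and any one counts.
- *That the before-after tests are offered as proof of efficacy despite natural recovery.* Section 8 does say that "Potential spontaneous recovery at the early stage of stroke may have the confounding effects on this trial", but the same sentence relies on the waiting-list arm to reduce this. Between-group comparisons are planned separately, and nowhere are within-group tests said to establish efficacy.
- *That choosing the test by a normality check is itself an error.* It is common practice. Preferring one model fixed in advance is a matter of judgement.

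**Conclusion.** The concern holds for the two test names: both are wrong as written, and nothing elsewhere in the article repairs them.

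- **Within groups:** the cost is lost power, not excess false positives. Its size depends entirely on the before-after correlation, which the documents do not give; with a correlation near zero there is almost no loss.
- **Between groups:** the fault is the missing three-group test together with unnamed, unadjusted pairs. The error rate of 8% to 12% is for one outcome at one visit, and assumes that any single significant pair would be read as a positive finding.

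The point should be fixed, but it is not critical. Both tests are conditional fallbacks, and a within-group test does not estimate the randomised effect.

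**What to change.** In section 7.5, and in the statistical analysis plan if it repeats the wording:

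1. For non-normal within-group comparisons, replace the Wilcoxon rank sum test with the Wilcoxon signed-rank test.
2. For the three-arm fallback, replace the Mann–Whitney U test with Kruskal–Wallis, followed by pairwise Mann–Whitney tests.
3. Name the pairs to be tested and state how multiplicity is controlled. The article at present speaks only of acupuncture against an unspecified control group, so the pairs have to be chosen, not merely referred to. In the no-difference simulation, either Bonferroni (4.0%) or requiring a significant Kruskal–Wallis test first (4.5%) kept the overall rate below 5%.

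The cost is a few sentences. No patients, visits or measurements are added.

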### Recruitment strategies and randomization

2.7

The study population is patients who had Post-stroke Cognitive Impairment with no dementia. We will recruit 360 eligible patients from five hospitals in China: The First Teaching Hospital of Tianjin University of traditional Chinese medicine (TCM), The Changchun hospital of TCM, Changzhi City of Traditional Chinese Medicine affiliated hospital, Changsha central hospital, The Second affiliated hospital of Baotou. Recruitment posters will be used in every participating hospital. We also use the various social media platforms to distribute the trial information. The eligible patients must satisfy the criteria defined below. Patients who express a general interest in taking part in the study will be informed of all necessary information in oral and written form. After fulfilling the criteria and signing the consent, the study personnel will assign the patient to the acupuncturist who is in charge of the patient.

A full-time staff of The First Teaching Hospital of Tianjin University of TCM will randomize all the eligible participants into the AG, NAG, or the WLG in a 1:1:1 ratio by a dynamic random allocation technique.

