### Outcome assessment

3.5

In this trail, most primary and secondary outcomes will be measured at baseline, the end of intervention(12weeks), after an additional 12-week follow-up period (24 weeks) and after an additional 24-week follow-up period (36 weeks). Amyloid-β and fMRI will be measured at baseline and the end of intervention. A summary of all the measures in the trial is summarized in Table 3.

**Table 3 T3:** Outcome measurements at each timepoint.

Study period	Enrolment	Intervention	Follow-up	
STUDY TIMES	The first time	The second time	The third time	The fourth time
TIME POINT	−3d-0	12 wks ± 3d	24 wks ± 3 d	36 wks ± 3d
MoCA	×	×	×	×
MMSE	×	×	×	×
CDR	×	×	×	×
NPI	×	×	×	×
WHOQOL-BREF	×	×	×	×
FAQ	×	×	×	×
β-Amyloid	×	×		
Adverse Reaction/Event		×	×	×
Vital signs	×	×	×	×
Recurrence		×	×	×
Using drugs	×	×	×	×
Laboratory examination	×	×		

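### Arms are compared by unadjusted analysis of variance although baseline scores and centre are available; the test is valid but gives up precision that costs almost nothing to recover

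*Protocol article*

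**What the plan says.** Section 7.5 of the protocol article names the between-arm test for continuous outcomes: "Variance analysis will be used for comparison between groups which is consistent with the normal distribution and homogeneity of variance". Where those conditions fail, the fallback is a rank-based test of the Mann–Whitney type, which takes no covariates. Baseline values are used only within arms, where "paired-sample *t* test will be used in intragroup comparison". No covariate is named there or elsewhere in the article.

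The design supplies information that this test does not use:
- Section 3.5: "most primary and secondary outcomes will be measured at baseline, the end of intervention", and again at weeks 24 and 36. Table 3 lists MoCA, MMSE, CDR, NPI, WHOQOL-BREF and FAQ at all four visits.
- Section 2.7: "We will recruit 360 eligible patients from five hospitals in China", allocated "in a 1:1:1 ratio by a dynamic random allocation technique". The article does not name the factors, if any, that the scheme balances.

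On sizing, section 7.5 says: "The sample size calculation is based on the improvement of Montreal cognitive assessment scale (MoCA) scores". It does not say whether the analysis of variance is run on follow-up scores or on changes from baseline.

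**The concern.** A patient's baseline score usually predicts the later score on the same scale. An analysis of variance on follow-up scores leaves all of that predictable variation in the error term. One on change scores removes it only in part, because it forces a slope of one on baseline. Either way the confidence interval is wider than it need be.

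A second, conditional issue comes from the allocation. If a dynamic scheme balances factors that predict outcome, the arm difference varies less from trial to trial than the unadjusted standard error implies. The reported standard error is then too large and the true type I error falls below its nominal level.

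Precision and power are at stake, not validity: the randomised comparison remains unbiased.

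**Working it through.** **Inputs from section 7.5.** Difference 0.6 MoCA points; SDs 1.13 and 1.20; 95 analysed per arm; one-sided 0.025 for sizing and two-sided 0.05 for analysis (the same critical value, 1.96); stated power 95%; 20% dropout.

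**Assumed, because the article does not give them.** Baseline–outcome correlation r from 0.3 to 0.7; equal variance at baseline and follow-up; share R² of outcome variance explained by the balanced factors.

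**Step 1: the plan's own figure.**
- Pooled SD = √((1.13² + 1.20²)/2) = √1.358 = 1.166.
- Required n per arm = (1.13² + 1.20²) × ((1.960 + 1.645)/0.6)² = 98.07, so 99. With SD 1.13 alone it is 93. The stated 95 is therefore reproduced approximately.
- Power at 95 per arm: SE = 1.166 × √(2/95) = 0.169; 0.6/0.169 − 1.96 = 1.59; power = 94.4%.
- Dropout: 95/0.8 = 118.75, so 119; 3 × 119 = 357, as stated.
- Unadjusted 95% CI half-width = 1.96 × 0.169 = 0.331.

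**Step 2: effect of baseline adjustment.** If the planning SD is that of the follow-up score, ANCOVA multiplies it by √(1 − r²). If it is that of the change score, the factor is √((1 + r)/2).

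| r (assumed) | Half-width, SD of follow-up score | Power | Half-width, SD of change score | Power |
|---|---|---|---|---|
| unadjusted | 0.331 | 94.4% | 0.331 | 94.4% |
| 0.3 | 0.316 | 96.1% | 0.267 | 99.3% |
| 0.5 | 0.287 | 98.4% | 0.287 | 98.4% |
| 0.7 | 0.237 | 99.9% | 0.306 | 97.1% |

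At r = 0.5 both factors equal √0.75 = 0.866, so the choice of reading does not matter there. An unadjusted analysis would need 95/0.75, about 127 per arm, for the same width.

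**Step 3: omitted allocation factors.** If balanced factors explain a share R² of the variance, the unadjusted SE is too large by 1/√(1 − R²), and the true two-sided size is 2(1 − Φ(1.96/√(1 − R²))).
- R² = 0.05: SE ratio 1.03, size 0.044.
- R² = 0.20: SE ratio 1.12, size 0.028.
- R² = 0.30: SE ratio 1.20, size 0.019.

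Minimisation was also simulated (three arms, five centres, 285 patients, 1,500 repetitions), with centre explaining 5% of the variance and baseline 25%:
- Balancing on centre only: model SE 1.02 times the true SD of the estimate, size 0.045.
- Balancing on centre and dichotomised baseline: ratio 1.13, size 0.027. With adjustment: ratio 1.00, size 0.046.

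The 1.13 lies below 1.20 because balancing a normal baseline score split at its mean captures only 2/π of its share: 0.05 + 0.25 × 0.637 = 0.209, and 1/√0.791 = 1.12.

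In both settings the adjusted model SE was about 16% smaller than the unadjusted one. That figure already contains the gain from step 2, so the gains in steps 2 and 3 must not be added.

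**The case against.** The strongest reply is that this is a one-paragraph methods section in a journal article. Covariates and allocation factors are commonly left to the full protocol or the analysis plan, and naming analysis of variance does not forbid covariates. Part of this stands: it is no fault that the article does not list the allocation factors. But the article does name the test, its assumptions and a fallback. The fallback takes no covariates, and baseline is assigned to within-arm tests. That is a stated choice, which an analysis plan would carry forward unless it is changed.

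The second reply is that the gain may be small, and this stands as a limit. Several MoCA versions, restricted entry scores and early spontaneous recovery could all lower r. At r = 0.3 on follow-up scores the variance falls by only 9%. If change scores are analysed, baseline is already partly used, and the gain shrinks as r rises.

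A reader might infer more than the document supports, in three ways:
- **That the stated power fails.** Raw-score SDs of 2.0 or 3.0 would give unadjusted power of 54% or 28% (0.6 difference, 96 per arm). Neither SD appears in the protocol, and sizing is on improvement. These figures are hypothetical.
- **That the standard errors are certainly too large.** This depends on which factors are balanced and how prognostic they are, and the article states neither.
- **That false positives are inflated.** The distortion runs the other way.

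**Conclusion.** The point holds as a loss of precision. On the protocol's own SDs the unadjusted comparison already has about 94% power, so the omission does not make the trial underpowered on its own assumptions. Baseline adjustment would cut the CI half-width from 0.331 to about 0.29 at r = 0.5, a reduction of about 13%. Over r = 0.3 to 0.7 and both readings of the SD, the adjusted half-width lies between about 0.24 and 0.32, narrower than the unadjusted one in every case. The correlation is an assumption throughout.

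The allocation effect is conditional: about 2% on the standard error if only centre is balanced, and about 13% if a strong factor such as dichotomised baseline score is balanced too (assumed R² of about 0.3 in total). Both effects are conservative; neither biases the estimate or raises the type I error. The change is worth making because it costs almost nothing, not because the stated analysis is wrong.

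**What to change.** Replace the between-arm analysis of variance with one of these:
- an ANCOVA of the follow-up score on arm, baseline score, centre and whatever factors the dynamic allocation uses; or
- a repeated-measures mixed model over weeks 12, 24 and 36 with the same covariates.

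Report adjusted arm differences with 95% CIs, and use the same model for MoCA, MMSE, FAQ and WHOQOL-BREF. Name the allocation factors where the model is specified, and fix the covariate list before unblinding so that it cannot be chosen from the results.

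The cost is a few lines of text and little analysis work. Baseline scores and centre are already recorded, and any allocation factors must be known in order to allocate. No extra patients, visits or measurements are needed. Which time point and which pair of arms are primary is a separate matter, which this change does not settle.

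### The between-arm test and the summary measure are chosen from the collected data, so the MoCA result may not be a mean difference comparable with the 0.6 points used for sizing

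*Protocol article*

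**What the plan says.** All of this stands in section 7.5 (Sample size and statistical methods) of the protocol article.

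- **Between-arm test.** ANOVA applies on two conditions: "Variance analysis will be used for comparison between groups which is consistent with the normal distribution and homogeneity of variance; if not, then" comes the alternative, "if not, then Mann–Whitney *U* test will be used".
- **Summary measure.** Mean and SD are given for normal data; otherwise "if they are not normal distribution, median (quartile interval) [M(IQR)] will present them".
- **Sizing.** "The sample size calculation is based on the improvement of Montreal cognitive assessment scale (MoCA) scores". A published study is cited for a difference of 1.5 points "with a standard deviation of 1.13 in AG and 1.20 in CG". The sponsor's own earlier work is then cited to say that "acupuncture treatment can probably improve the MoCA by 0.6 on average compared with control group". The result: "Considering a 1-sided significance level of 0.025 and power of 95%, 95 participants are required for each group".

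The section names no normality check, no variance check and no threshold. It does not say whether the check is made per arm or on residuals.

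**The concern.** The sample size is built on a difference in mean MoCA improvement. The analysis rule then lets the collected data decide whether a mean difference is tested and reported at all. Three consequences follow.

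1. The rank test does not test equality of means and gives no estimate in MoCA points. If the fallback applies, the report may hold two medians and a P value, with nothing to compare with 0.6.
2. The rule applies to each continuous outcome at each visit. Table 3 lists six scales (MoCA, MMSE, CDR, NPI, WHOQOL-BREF, FAQ) at three post-baseline visits, which is 6 × 3 = 18 outcome-by-visit comparisons. The effect measure could change from one to the next, so that MoCA at 12 weeks and at 36 weeks are not on the same footing.
3. Unequal variance also sends the analysis to the rank test, but a rank test is no remedy for unequal variance.

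These points would stand whichever rank test was named as the fallback.

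**Working it through.** **Inputs from section 7.5.** Difference 0.6; SDs 1.13 and 1.20; one-sided 0.025; power 95%; 95 per group; 20% dropout.

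**The plan's own figure.** Pooled SD = √[(1.13² + 1.20²)/2] = √1.358 = 1.166. Then n = 2(1.960 + 1.645)² × 1.358 / 0.6² = 98.1, so 99 per group (100 with the t distribution). The printed 95 is not reproduced with both SDs; SD 1.13 alone gives 93 (94 with t). Power at 95 is about 94%, so the gap is small and does not affect this point. The dropout step reproduces: 95/0.8 = 118.75, rounded up to 119, and 3 × 119 = 357.

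**Does the variance condition fail on the stated SDs?** Variance ratio = 1.20²/1.13² = 1.128. At 95 per arm the F test gives p = 0.56; about 1,100 per arm would be needed for p < 0.05. In simulation Levene's test rejects in 6–7% of trials. The stated SDs do not trigger the fallback.

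**Does the normality condition fail?** Simulation of three arms of 95, underlying scores exactly normal, checks at the 5% level. The type of check is an assumption. So is the scoring in whole points, and so are the SDs of 2, 3 and 4.

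| Scores | SD | Normality check | ANOVA runs |
|---|---|---|---|
| Continuous | 1.13/1.20/1.20 | Shapiro–Wilk per arm | 79% |
| Continuous | same | Lilliefors per arm | 81% |
| Continuous | same | Shapiro–Wilk on residuals | 88% |
| Continuous | same | plain Kolmogorov–Smirnov | 93% |
| Whole points | same | any of the three per-arm tests | 0% |
| Whole points | same | Shapiro–Wilk on residuals | 0.9% |
| Whole points | 2 | Shapiro–Wilk per arm | 0.2% |
| Whole points | 3 | Shapiro–Wilk per arm | 41% |
| Whole points | 4 | Shapiro–Wilk per arm | 64% |

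The whole-point rows at the plan's SDs have a simple cause. An arm of 95 then holds only about 7 distinct values, and a normality test reacts to that coarseness even when the underlying score is normal.

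**What does the switch do to error rates?** AG against one control group, 95 per arm, SDs 1.13 and 1.20, two-sided 5%, 6,000 runs:

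| Scores | True difference | t test | Mann–Whitney |
|---|---|---|---|
| Continuous | 0.6 | 94.1% | 92.9% |
| Whole points | 0.6 | 93.1% | 91.8% |
| Continuous | 0 | 4.8% | 5.2% |
| Whole points | 0 | 5.0% | 4.8% |

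Applying the switching rule itself (Shapiro–Wilk plus Levene) with equal means at the plan's SDs gives 4.8–5.0%, with normal or left-skewed errors.

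**Where would the rank test mislead about means?** The plan's SD ratio is 1.20/1.13 = 1.06. With equal means, left-skewed errors and an assumed SD ratio of 1.5 or 2, Mann–Whitney rejects in 17–19% or 32–34% of trials at nominal 5%; Welch's test stays at about 5–6%. With normal errors and a ratio of 1.5, Mann–Whitney rejects in only about 5.5%. The inflation needs both skew and a large variance imbalance.

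**The case against.** The strongest reply is that the rule is written down in advance and does no measurable damage on the plan's inputs: type I error and power are almost the same on either branch. That is correct, and it limits the finding. A pre-stated rule is still not a pre-stated test or effect measure, because which branch applies is known only from the outcome data.

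A second reply is that a fuller analysis plan may name the normality check and its threshold. It may, and their absence from an article is not the complaint. Naming them would leave the data-driven choice in place, and that choice is what the article prints.

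A third reply is that if normality tests always reject at these SDs, the method is in effect fixed. Under those assumptions it is, but it is then fixed on a rank test and a median, away from the mean difference used for sizing. At larger SDs the choice varies by chance. Neither case serves the trial.

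Three stronger readings are tempting and are not supported:

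- **That ANOVA would never run.** This needs whole-point scores with SDs near 1.13–1.20 and a formal normality test, and the article states neither the scoring unit of the change nor the test. With near-continuous scores ANOVA runs in 79–93% of simulated trials, and a graphical check could also retain it.
- **That the trial is sized on ANOVA.** Section 7.5 gives a two-group mean difference and two SDs, and states no ANOVA calculation.
- **That false positives will be inflated to 17–34%.** This needs skew with SD ratios of 1.5–2, against 1.06 in the plan.

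**Conclusion.** The concern holds as a fault of pre-specification and estimand. For MoCA and every other continuous outcome, section 7.5 leaves both the between-arm test and the summary measure to be settled by the collected data. The trial may therefore report no estimate comparable with its 0.6-point planning difference.

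How often the rank branch would be taken cannot be known from the article. It is nearly always under whole-point scoring, the plan's SDs and a significance test of normality; largely a matter of chance at assumed SDs of 3–4; and a minority of trials (about 7–21%) if scores behave as continuous and normal.

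The size in error-rate terms is negligible on the plan's figures: type I error about 5%, and whole-point power about 92% for ranks against 93% for means. The point should be corrected, but it does not threaten the sample size.

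**What to change.** In section 7.5, delete the rule that switches test and summary on the distribution checks. Pre-specify one between-arm method for MoCA and the other continuous scales: a linear model reporting mean differences with 95% CIs and variance-robust (Welch or sandwich) standard errors, used whatever the normality and variance checks show. Report means and SDs for all scales at all visits; medians and quartiles may be added. Keep a rank-based comparison as a labelled sensitivity analysis.

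The cost is wording only. No new data or patients are needed, and with about 95 per arm a comparison of means is reliable without normality.

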### Primary outcome

3.6

The primary outcome of this study is the cognitive function and incidence of PSD.

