### Incidence of PSD

3.8

We will use MMSE, which is the most widely used by frontline physicians, to detecting dementia. Dementia: MMSE score ≤17 (illiteracy), or MMSE score ≤20 (primary school culture), or MMSE score ≤24 (middle school and above).^[33]^

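### Incidence of PSD, part of the primary outcome, has only an unadjusted χ² test stated for it; a visit-based model adjusted for baseline MMSE would use data already collected and resist unequal loss

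*Protocol article*

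**What the plan says.** Section 3.6 of the protocol article states: "The primary outcome of this study is the cognitive function and incidence of PSD". Section 3.8 defines the event by the MMSE: "We will use MMSE, which is the most widely used by frontline physicians, to detecting dementia". The cut-offs depend on education (17, 20 or 24) and are repeated in section 2.5. Section 2.3 admits only patients scoring above those same three numbers.

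Table 3 schedules the MMSE at baseline and at weeks 12, 24 and 36. Section 3.4 stops follow-up for a patient who does not respond for a week or declines. Section 9 keeps the available data of patients who withdraw.

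For categorical results, section 7.5 offers one method: "Group comparisons will then be undertaken using χ^2^ tests for categorical characteristics". A two-sided P below .05 "represents statistical significance for all the analyses". The other listed methods (paired t, Wilcoxon, variance analysis, Mann–Whitney) are for continuous variables. Section 7.5 also says "we assumed the dropout rate of 20" per cent. It gives no event rate, sample size or power for PSD.

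**The concern.** PSD is looked for up to three times. A patient lost after week 12 has had one chance to be counted and a completer has three. A proportion over all randomised patients treats the lost patient as event-free after the last visit. A proportion over completers discards events seen before loss. A χ² test on either proportion does not use the number of visits attended.

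The test also ignores baseline MMSE. Entry and endpoint share their cut-offs, so a patient who enters one point above the cut-off is closer to the event than one who enters six points above it.

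At stake is the claim that section 8 presents as new, namely prevention of progression to PSD. Unequal loss could bias that comparison, and ignoring a prognostic baseline value could waste power.

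**Working it through.** **1. The plan's own figure.** Section 7.5 states "Considering a 1-sided significance level of 0.025 and power of 95%, 95 participants are required for each group", with "acupuncture treatment can probably improve the MoCA by 0.6 on average compared with control group" and "with a standard deviation of 1.13 in AG and 1.20 in CG".

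n = (z₀.₉₇₅ + z₀.₉₅)² × (SD₁² + SD₂²) / δ² = (1.960 + 1.645)² × (1.13² + 1.20²) / 0.6² = 12.995 × 2.717 / 0.36 = 98.1, so 99 per group.

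With 1.13 for both groups the result is 93. Power at 95 per group with both SDs is 94.4%. The stated 95 is therefore close. Dropout: 95 / 0.8 = 118.75, so 119, and 3 × 119 = 357, as stated. This calculation concerns MoCA only. Everything below uses 120 per arm (360 / 3), one pair of arms, and assumed PSD rates.

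**2. χ² under no effect, all randomised in the denominator.** Let h be the hazard per visit, the same in both arms, and d the total loss by week 36, spread evenly, so that retention per visit is r = (1 − d)^(1/3).

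Observed incidence = h × [r + r²(1 − h) + r³(1 − h)²].

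Example with h = 0.07 (true incidence 19.6%):
- d = 10%: r = 0.9655, observed 18.3%.
- d = 30%: r = 0.8879, observed 15.6%.
- Spurious risk ratio 0.1828 / 0.1559 = 1.17.
- Standard error about 0.0484, so rejection probability = Φ((0.0269 − 1.96 × 0.0484) / 0.0484) + Φ((−0.0269 − 1.96 × 0.0484) / 0.0484) = 0.080 + 0.006 = 8.6%.

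| Loss in the two arms | True PSD 8.7% | 19.6% | 31.9% |
|---|---|---|---|
| 20% v 20% | 5.0% | 5.0% | 5.0% |
| 15% v 25% | 5.4% | 5.9% | 6.6% |
| 10% v 30% | 6.5% | 8.6% | 11.6% |
| 5% v 35% | 8.3% | 13.3% | 20.1% |

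The arm with more loss shows fewer events. Heavier waiting-list loss would therefore work against acupuncture.

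**3. Simulation from a hazard** (1,000 runs per setting, true control incidence about 20% to 27%, baseline distance 1 to 6 points). The model is a discrete-time complementary log-log hazard with arm, visit and baseline distance. Power is at hazard ratio 0.5. The slope is the assumed change in log hazard per point of baseline distance.

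| Loss | Slope | χ² all: size / power | χ² completers: size / power | Model: size / power |
|---|---|---|---|---|
| 20% v 20% | 0 | 3.8 / 45.2% | 4.2 / 43.1% | 3.5 / 43.5% |
| 20% v 20% | 0.3 | 4.3 / 48.0% | 4.4 / 44.4% | 3.5 / 48.4% |
| 20% v 20% | 0.6 | 6.1 / 53.1% | 4.7 / 48.8% | 4.4 / 60.8% |
| 10% v 30% | 0 | 10.7 / 29.4% | 6.3 / 46.5% | 5.9 / 46.2% |
| 10% v 30% | 0.3 | 10.0 / 28.7% | 5.9 / 47.2% | 5.3 / 50.2% |
| 10% v 30% | 0.6 | 10.9 / 29.9% | 6.3 / 49.7% | 5.7 / 60.5% |

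The Monte Carlo standard error is about 0.7 points at 5% (√(0.05 × 0.95 / 1000)) and 1.6 points at 50%. At equal loss the same model without the baseline term has power 43.8%, 47.0% and 51.6%, which is no better than χ².

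**4. Simulation from MMSE crossing the cut-off.** Assumed: baseline distance 1–6 points in 60% and 1–9 in 40%, patient SD 1, visit noise SD 1.5. Ranges cover several independent codings of this set-up, with the model against χ² over all randomised.
- Equal 20% loss, 0.6-point MMSE benefit: χ² 22% to 26%, model 27% to 36%.
- Equal 20% loss, 1.0-point benefit: χ² 52% to 54%, model 67% to 69%.
- 10% v 30% loss: χ² size 6.4% to about 8%. Power at 0.6 points is 13% to 17% against 34% to 36%.

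**5. Loss related to outcome.** No effect, 20% random loss in both arms, and 25% of control-arm PSD cases leaving before detection: size 12.4% for χ² and 11.8% for the model.

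**The case against.** Section 7.5 speaks of categorical characteristics and never names PSD, and a condensed article may leave the denominator, missed visits and covariates to a fuller document. That stands as far as it goes, and the absence of those details is not the point here. The point is the stated method: nothing else in section 7.5 fits a binary outcome.

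A reader might infer that baseline distance biases the comparison. It does not. Section 2.7 randomises patients, so the distance is balanced in expectation and ignoring it costs power only. How much it costs depends on how prognostic the distance is, which the documents do not say.

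A reader might also infer that 20% dropout by itself invalidates χ². It does not: with equal loss unrelated to outcome the test keeps its 5% level. The documents give one overall dropout figure and no split by arm. Section 3.4 offers acupuncture after follow-up to limit loss. Section 2.8 keeps needled patients unaware of their group, so no reason for unequal loss between the real and sham arms is stated. Unequal loss remains plausible for the waiting list, which is unblinded and gets only standard treatment for 36 weeks (section 3.3). A completers-only χ² holds its size at about 6% at 10% v 30% when loss is unrelated to outcome, so the inflation belongs to the all-randomised denominator.

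Finally, the model does not cure everything. Section 2.6 ends participation for a deteriorated condition, and step 5 shows that censoring such patients leaves nearly the same error as χ².

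**Conclusion.** The point holds as a cheap improvement to the stated test, not as a demonstration that the χ² result would be invalid.

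- Equal, non-informative loss: χ² is valid. Adjusting for baseline MMSE distance gains about 0 to 15 points of power: −2 to 8 in step 3 and 5 to 15 in step 4. The gain comes from the covariate. The visit structure alone adds none.
- Unequal loss with all randomised in the denominator: χ² is biased. At an assumed 10% v 30%, simulated size is about 6% to 11% (up to 11.6% in the closed form). In step 3, power is 29% to 30% against 46% to 61% for the model.
- Outcome-related withdrawal: neither method is protected.

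It would be too strong to say that the model makes PSD adequately powered. Even 20% v 10% gives χ² power of only 58% at 120 per arm, and the sample size rests on MoCA. Nor do the documents say that PSD events will be few: the only dementia rate is a 10-year background figure in the introduction. Event rates, loss splits, baseline slopes and MMSE noise are all assumptions.

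**What to change.** For PSD, replace χ² in section 7.5 with a discrete-time model (logistic or complementary log-log) over weeks 12, 24 and 36. Include arm, visit and baseline MMSE distance from the education-specific cut-off, and censor patients at their last attended visit. Report Kaplan-Meier cumulative incidence at week 36 by arm. Add a sensitivity analysis for participants withdrawn for a deteriorated condition, since censoring assumes that loss is unrelated to outcome. χ² can stay for baseline categorical descriptors.

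The cost is a sentence or two in the methods and one extra analysis. Table 3 already schedules the MMSE at every visit needed. The treatment effect becomes a model-based hazard or odds ratio instead of a raw difference in proportions, but the Kaplan-Meier figures keep an absolute comparison in view.
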